### Informed consent

The researcher will arrange a mutually convenient date and venue for patients to give consent for the trial. This should typically happen within 10 days of invitation, to enable participants to be allocated to the respective group with sufficient time before their start of radiotherapy. The patient’s written consent will be obtained using the study consent form. Baseline measures will then be completed and the allocation decided via a central randomisation service. The researcher will explain and leave the appropriate study pack with the participant.

### Group allocation

The nature of the intervention means it will not be possible to blind either the researcher or participants to their arm allocation. Analysis of outcome measures will be conducted blind to participant allocation where possible. Randomised group allocation and retention of randomisation codes will be via a central online database service [www.sealedenvelope.com] [21]. This remote allocation service removes the possibility of the researcher influencing group allocation. Allocation to the behavioural intervention arm will be in the ratio 2:1 using a permuted block protocol. A stratification variable will be age (< 57 years and ≥ 57 years). The researcher will inform the psychology team delivering the intervention of patients allocated to the intervention arm as soon as practically possible via a standard referral form. These participants will then be discussed at a psychology team meeting before allocation to one of the two interventionists.

### The behavioural intervention

The intervention was developed by [name] and King’s College London psychology colleagues [14]. Elements are informed by a CBT model of symptom management—the objective being to self-manage fatigue by altering associated thoughts and behaviours. Elements of MI will be incorporated to make sure that individual needs are the starting point to encourage movement towards behavioural goals [16, 17]. The reward (reinforcement) is that in the future the participant may have less fatigue.

The function of the intervention is to motivate helpful behaviour change. The intervention is built on four main components:*Education*—written and verbal information about fatigue to increase understanding of fatigue, its causes and consequences. The education content is informed by the Macmillan Cancer Support booklet ‘Coping with Fatigue’ [22];*Motivation to change*—the counsellor works to promote self-efficacy and uses persuasive motivational language and assesses the participants’ commitment/readiness to change;*Goal setting* and behavioural regulation through self-monitoring of behaviour—to help people plan for and achieve the future goals that are meaningful to the person’s life. These goals may be adjusted with time. All intervention participants will be asked to wear a physical activity monitor, which may be used to set and monitor activity goals according to individual preference;*Emotional support*—to help anticipate any negative emotions/barriers (positive language is used to stimulate positive feelings, motivation and importantly enable action.)

​The intervention has been coded by a psychologist using the Behaviour Change Taxonomy (BCT) (http://www.bct-taxonomy.com/), which has been developed to identify the active components of behavioural change interventions [23]. The key components are:​Used a lot throughout: knowledge, goals and behavioural regulation;Moderate use of: intentions, reinforcement, emotion;Some use of: beliefs about capabilities, optimism, beliefs about consequences;And a little use of: professional role and identity and social influences.

The intervention will be delivered on an individual basis. It comprises three 60-min sessions per participant. The sessions (Table 1) will be delivered face-to-face in the psychology department counselling room at the cancer treatment centre and scheduled to coincide with treatment appointments at crucial phases in the treatment pathway: (i) start of week one of radiotherapy, (ii) fatigue intensifies after 10 fractions and (iii) treatment finishes after 15 fractions (or 20 fractions if a tumour-bed boost has been prescribed). One of two professionals attached to the local psychology team (JA and MS) will deliver the sessions. JA is an experienced counsellor and MS is a review radiographer who works holistically with patients during their radiotherapy. A skeleton plan provides some standardisation of session components. Within this structure, the content of the sessions is adaptable to make sure the interaction meets individual needs. Where a patient has routinely completed a holistic needs assessment, this information will help initiate this process of individualisation.

**Table 1 Tab1:** Summary of intervention components

Time	Content	Behaviour change technique/construct/label
Call 0 After randomisation	Brief scene setting telephone call Introduce counsellor. Prepare for sessions and agree dates for future sessions	
Session 1 Within first few RT treatments	Assessment of current energy state Clarify patterns, causes and impacts of fatigue Identify individual goals and concerns and the meaning of fatigue for this person’s life during RT Assess readiness to change Consider barriers to change *Set three ‘SMART’ goals* • *Activity and sleep diaries and booklet* • Education about fatigue and radiotherapy • Emotional support and encouragement	KNOWLEDGE—of antecedents and health consequences EMOTION—self-assessment of affective consequences BEHAVIOURAL REGULATION—self-monitoring of behaviour BELIEFS ABOUT CAPABILITIES—verbal persuasion to boost self-efficacy Goal setting (outcome and behaviour) Action planning (including implementation intentions
Session 2 Week 2 of radiotherapy	Review of fatigue state Review of diary Guidance with how to manage fatigue and meet goals Prioritisation of activities Best utilisation of upcoming radiography review clinic	GOALS—review of outcome and behaviour goals BEHAVIOUR REGULATION—self-monitoring of behaviour BELIEFS ABOUT CONSEQUENCES—comparative imagining of future outcomes INTENTIONS—commitment GOALS—review of outcome goals Increased self-efficacy, control and positive mood
Session 3 Week 3 of radiotherapy	*Looking to end of treatment and beyond* *Weekly planner and diary review* Modification of activity and goal scheduling *Positivity* *Self-efficacy* *Social support*	BEHAVIOUR REGULATION—self monitoring of behaviour GOALS—review behaviour goals Goal setting—outcome and behaviour goals Encourage self-monitoring and modification of goals; INTENTION—commitment Identification of ambivalent/unhelpful thoughts about end of treatment and beyond; enhancement of approach coping by adopting alternative thoughts Incremental increase in activity levels to achieve goals; normalisation after treatment OPTIMISM—verbal persuasion to boost self-efficacy EMOTION—reduce negative emotions SOCIAL INFLUENCES—social support or encouragement (general)

#### Quality assurance of the behavioural intervention

Intervention training will include the theoretical basis for the intervention and a detailed overview of the manual. The counsellor will record the use of goal setting, activity monitors and any other relevant use of the intervention. Sessions will be audio-taped to enable integrity-to-manual checks. An independent assessor will evaluate fidelity and the extent to which the underlying theory is used for the first three intervention sessions and a random selection of later sessions.

### The ‘education alone’ intervention

Participants allocated to the ‘education alone’ trial arm will be given the Macmillan Cancer Support booklet called *Coping with Fatigue* [22]. This booklet is freely available at information stands within the cancer centre. The content provides information about fatigue and suggests ways of coping with it.

### Fatigue risk score validation group

Participants who are predicted to be at a low risk of fatigue will be allocated to a validation group. These women will fill in a Functional Assessment of Chronic Illness Therapy (FACIT-F) Fatigue Scale [24] on the last day of their treatment and at 10 days and 6 months after their radiotherapy finishes. Any patients estimated to be at a higher risk of fatigue who have declined entry into the feasibility trial will be offered the opportunity to enter the validation group. The fatigue data from the trial control arm participants will also be included. The group data will be correlated to the fatigue risk score calculated before treatment and thereby enable an assessment of the accuracy of the prediction tool. Analysis will be stratified by prior chemotherapy/no chemotherapy. The predictive ability of the tool will be evaluated with a view to potential use in selecting participants in an effectiveness trial.

### Study assessments

#### At screening

The patient’s cancer diagnosis and reasons for ineligibility will be recorded. A screening log will be maintained that records the numbers of people who:Are eligible/ineligible;Are approached;Decline to be contacted and reasons for declining (if proffered);Score above and below the fatigue score threshold;Decline at the point of consent or trial group allocation.

#### Trial group baseline measures

Baseline outcome measures should be completed directly after consent and prior to random allocation to a trial arm. This will either happen at the cancer centre or the person’s home, depending upon individual preference. The following demographic and clinical data will be recorded on the pre-treatment case report form (CRF) before randomisation:Date of birth and postcode;Cancer diagnosis and pathological stage and grade;Employment status;Adjuvant therapies prescribedHistory of previous or concurrent treatments for this cancer—surgery, chemotherapy, endocrine therapy;Other relevant medical health history including mental health issues.

#### Trial outcome measures

The feasibility outcomes will include an evaluation of outcome measure completion rates. Outcome measures include Functional Assessment of Chronic Illness Therapy Fatigue Scale (FACIT-F) [24], Hospital Anxiety and Depression Scale (HADS) [25], European Organisation for Research and Treatment of Cancer quality of life physical functioning subscale (EORTC-QLQc30 version 3.0) [26], physical activity as measured by the Fitbit Alta activity tracker and Amy Hoffman’s Self-Efficacy for Managing Chronic Disease scale [27]. The primary endpoint is fatigue as measured by the FACIT-F 10 days after the completion of radiotherapy. Analysis will be stratified by prior chemotherapy/no prior chemotherapy.

The schedule of outcome measures is shown in Table 2. Scale outcome measures will be self-reported by participants (presumed to be at their home). One phone call will be made to prompt a response if outcome measures have not been returned within 7 days of being due. If participants discontinue with intervention, then any completed outcome measurements will be retained for analysis with participant consent.

**Table 2 Tab2:** Schedule of trial outcome measures

Outcome measure	Pre-RT	Week 2	Week 3	+ 10 days	+ 3 weeks	+ 6 months
		After 10 fractions of RT	After 15 fractions of RT	10 days after RT	3 weeks after RT	6 months after RT
	Baseline	On treatment			Follow-up	
	T0	T1	T2	T3	T4	T5
FACIT-F	X	X	X	X	X	X
HADS	X			X		X
Physical activity		X	X			
EORTC-QLQc30	X		X	X		X
Amy Hoffman’s self-efficacy	X		X	X		

### Trial process evaluations

The feasibility and acceptability of the trial processes will be evaluated with mixed-methods.

#### Evaluation of the feasibility of the trial

Eligibility rate will be calculated as the proportion of women with stage 0–IIIa breast cancer on radiotherapy clinic lists who also meet the eligibility criteria;Recruitment rate will be calculated as the number of people who consent to participate divided by the number of eligible patients approached;Eligible patients who decline to enter will be asked to volunteer a reason;Retention rate will be calculated as the number of participants who complete all outcome measures divided by the number who record baseline outcome measures;Adherence to the intervention will be monitored by recording the number of sessions completed;Reasons for discontinuation or non-adherence should be sought, where possible.

The definitive trial will be considered feasible if > 70% of participants complete all the interventions and outcome measures. If this rate is between 65 and 70%, then adjustments in future work should be considered. A rate < 65% requires substantive change to the intervention and/or to the trial process.

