### Sample size

We aim to recruit approximately 77 participants across all study groups. Assuming a 10% loss to follow-up, this will yield final sample sizes of 20, in the intervention group, and approximately 10 and 40 in the control and fatigue risk score validation groups, respectively. These figures are based on logistical grounds and are informed by previous experience in this setting. Assuming a 50% recruitment rate, we would need to approach about 160 eligible women across the 12-month study duration to achieve our planned sample. Recruitment will close when 20 participants have been recruited to the intervention arm.

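### The stated recruitment rate pools randomised women with validation-only women, so it does not estimate willingness to be randomised

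*Protocol article*

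**What the plan says.** Under Evaluation of the feasibility of the trial, the protocol article gives its only definition of recruitment: "Recruitment rate will be calculated as the number of people who consent to participate divided by the number of eligible patients approached". The definition does not say which group the consenting women join.

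The Sample size section shows how the rate is used in planning. It states "We aim to recruit approximately 77 participants across all study groups". After allowing for 10% attrition, it expects to end with 20 women in the intervention arm, about 10 controls and about 40 validation women. On the number to approach, it says: "Assuming a 50% recruitment rate, we would need to approach about 160 eligible women across the 12-month study duration to achieve our planned sample".

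The Fatigue risk status section randomises only women scoring 5 or more, expects about half of patients to reach that score, and sends women scoring below 5 to the validation group with a consent form of their own. Women at or above the threshold who refuse the trial are not lost to the study. The validation group section makes room for them there: "Any patients estimated to be at a higher risk of fatigue who have declined entry into the feasibility trial will be offered the opportunity".

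Under Recruitment process, risk is scored only once a woman has said she wishes to take part. The screening log, under At screening, counts women approached, women above and below the threshold, and those who "Decline at the point of consent or trial group allocation". The Data analysis section says the study should inform the decision to progress and estimate the unknown parameters needed for the effectiveness study. It plans recruitment rates with 95% confidence intervals.

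**The concern.** The study makes two very different requests. One is randomisation, with a one-in-three chance of receiving a booklet only, a two-in-three chance of three one-hour sessions, and six assessment points. The other is completing fatigue questionnaires around and after the end of radiotherapy. A single rate that counts consent to either says little about the first.

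Two features of the definition cause this. In the numerator, a high-risk woman who refuses randomisation but accepts the questionnaires counts as recruited, so her refusal leaves the rate unchanged. In the denominator, approach comes before risk scoring, so it includes women who will score below 5 and cannot be randomised whatever they wish.

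Willingness of high-risk women to be randomised is a core unknown for a feasibility trial whose purpose is to inform a definitive one. The only recruitment rate that the protocol defines does not estimate it.

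**Working it through.** **Inputs (protocol article).** Final sizes 20, 10 and 40, total 70; loss to follow-up 10%; target about 77; assumed recruitment rate 50%; about 160 to approach (all Sample size). About 50% scoring 5 or more (Fatigue risk status).

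**1. Reproduce the plan's figure and see which women it counts.**
- All groups: 70 × 1.10 = 77, or 70 / 0.90 = 77.8, rounded up to 78.
- Number to approach: 77 / 0.50 = 154, or 78 / 0.50 = 156. Both agree with about 160.
- Trial arms only: 30 / 0.90 = 33.3, and 33.3 / 0.50 = 67, which is far from 160.

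The 50% rate therefore works only with validation women in the numerator.

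**2. Share of approached women who would be randomised.** The number randomised is taken as 30 to 33.3. Sample size gives 20 in the intervention arm after attrition, but also closes recruitment once 20 have been recruited to that arm.
- Low: 30 / 160 = 18.8%.
- High: 33.3 / 154 = 21.6%.
- Ratio to the pooled rate: 50 / 18.8 = 2.7 and 50 / 21.6 = 2.3.

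For scale, Wilson 95% intervals are 42% to 58% for 77/154 and 16% to 29% for 33/154. The two quantities would be clearly distinct even at this sample size.

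**3. Where the gap comes from.** Suppose half of those approached are high risk.
- 30 / 80 = 37.5%, so 50 / 37.5 = 1.33.
- 33.3 / 77 = 43.3%, so 50 / 43.3 = 1.15.

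The overall factor is 2 × 1.33 = 2.7 or 2 × 1.15 = 2.3. The factor of 2 is risk prevalence. Only the remaining 1.15 to 1.33 is lower uptake of the trial among high-risk women.

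**4. Response of the pooled rate to refusal.** Take 160 approached and 80 consenting to something, 40 of them high risk. Assume that every high-risk woman who refuses the trial joins the validation group.

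| Accept randomisation | Pooled rate | Randomised / approached |
|---|---|---|
| 40 of 40 | 80/160 = 50% | 25% |
| 20 of 40 | 80/160 = 50% | 12.5% |
| 0 of 40 | 80/160 = 50% | 0% |

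This is the limiting case. Where some refusers also decline validation, the rate falls, but by less than trial uptake does.

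**5. Illustration of the consequence.** Assume a definitive trial of 300 randomised; this figure is not in the documents. A yield of 50% implies 300 / 0.50 = 600 to approach. A yield of 18.8% to 21.6% implies about 1,600 to 1,390.

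**The case against.** The feasibility definition names no group and stands under a heading about the trial. The retention rate beside it uses baseline measures, which are described only for the trial group, and the Informed consent section speaks of consent for the trial. A trial-only numerator is a fair reading of that section alone. It does not survive the Sample size arithmetic, which gives about 160 only when all groups are counted. Even if it were adopted, low-risk women would remain in the denominator.

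The screening log, with the randomisation count, holds what is needed to calculate the right rates. That stands: no information is lost. But a recoverable count is not a defined outcome, and the article does fix a definition.

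Three stronger readings are tempting and are not supported.
- A reader might infer that the plan misplans the definitive trial. No definitive sample size or criterion uses this rate, and use of the score to select participants for that trial is only a possibility. The understatement arises only if someone carries the pooled rate forward as the randomisation yield.
- A reader might put the whole 2.7 down to refusal. It is the top of a range, and most of it is the expected half scoring below 5, a share that the study will itself measure.
- A reader might infer that the trial could be declared feasible however many refuse, because the completion thresholds omit recruitment. The Data analysis section brings recruitment rates into the evaluation that informs progression. Heavy refusal would also show as delay in filling the intervention arm.

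**Conclusion.** The concern holds as a fault in the definition of one feasibility outcome. Read with the Sample size and risk score sections, the stated rate mixes two kinds of consent and has a denominator that includes women who cannot be randomised. It does not estimate willingness to be randomised. On the plan's own figures, 50% as defined corresponds to about 19% to 22% of approached women randomised. The possible understatement of the number to approach, by a factor of about 2.3 to 2.7, depends on the pooled rate being reused as a randomisation yield under the same approach-then-score pathway.

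The size rests on the plan's approximate figures, on 30 to 33.3 women randomised and, for the split by cause, on half of the approached women being high risk. The complete insensitivity to refusal further requires that all refusers accept the validation group, which they are only offered.

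**What to change.** In the feasibility section, replace the single rate with a chain, each step with a 95% confidence interval:
- agreed to risk screening / eligible women approached;
- scored 5 or more / scored;
- randomised / scored 5 or more and offered the trial;
- randomised / eligible women approached.

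Leave validation-only entrants out of the trial recruitment numerator and report validation uptake separately, distinguishing low-risk women from high-risk women who declined the trial. In Sample size, say that the 50% refers to consent to any group.

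Use the whole chain when judging feasibility and planning the definitive trial. The third step alone would mislead in the other direction, because risk is scored only in women who already wish to take part. With 80 consenting and half of them high risk, 30 randomised gives 30/40 = 75%, which omits everyone who refused before scoring.

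The cost is a change of wording and a little more reporting. The counts come from the screening log and the randomisation record, so no new data are needed. The per-approach randomisation figure will look less favourable than the pooled rate.

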**Methods:**

A pragmatic single-site non-blinded feasibility trial of a behavioural intervention. Main inclusion criteria are prescription of the UK standard 40 Gy in 15 fractions over 3 weeks of radiotherapy (± tumour bed boost) for early (stage 0–IIIa) breast cancer. The total projected sample size after attrition is 70. A previously developed fatigue risk score tool will be used to predict individual’s likelihood of experiencing fatigue. Thirty women predicted to be at a high risk of experiencing significant fatigue will be allocated in the ratio 2:1 to the behavioural intervention or education trial arms, respectively. These feasibility trial participants will be assessed at baseline, after 10 and 15 fractions of radiotherapy and 10 days, 3 weeks and 6 months after radiotherapy. A further 40 women predicted to be at a lower risk of fatigue will join a risk score validation group.

Measures to assess feasibility include recruitment, retention and completion rates and variation in implementation of the intervention. Process evaluation with intervention providers and users includes fidelity and adherence checks and qualitative interviews to understand how changes in behaviour are initiated and sustained.

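### The feasibility rule is set on all participants, so controls, who have no sessions to miss, can lift an intervention arm below the plan's own cut-point to a feasible verdict

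*Protocol article*

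**What the plan says.** The section on evaluating the feasibility of the trial gives one three-zone progression rule. The definitive trial counts as feasible if more than 70% "of participants complete all the interventions and outcome measures". It continues: "If this rate is between 65 and 70%, then adjustments in future work should be considered", and "A rate < 65% requires substantive change to the intervention and/or to the trial process". No arm is named.

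The Abstract fixes the group to which the rule would apply: "Thirty women predicted to be at a high risk of experiencing significant fatigue will be allocated in the ratio 2:1", to behavioural intervention or education. It then calls these women the feasibility trial participants, as does the Study design section.

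The two arms have very different tasks. For the behavioural intervention: "It comprises three 60-min sessions per participant", delivered face to face. Women in the education-alone "trial arm will be given the Macmillan Cancer Support booklet called" *Coping with Fatigue*, and nothing more. The heading of that section nevertheless calls the booklet an intervention, so the plural in the progression rule naturally covers both arms.

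The same feasibility section also defines a retention rate (all outcome measures completed, out of those with baseline measures) and an adherence record (number of sessions completed). The Data analysis section reports retention and adherence with 95% confidence intervals. Neither has a threshold of its own.

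**The concern.** The Abstract gives the trial's purpose as judging whether the intervention can be delivered in the radiotherapy pathway, and the Data analysis section says the study is to determine whether to move on to an effectiveness trial. The three-zone rule is the only stated numerical basis for that decision.

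One third of its denominator consists of women who have no sessions to attend. They can fail only by missing questionnaires. If controls complete more often than intervention women, the pooled rate overstates completion where completion is hardest, and the study could be called feasible when the arm carrying the intervention falls below the plan's own cut-points.

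**Working it through.** **Inputs.** Cut-points of 65% and 70% (feasibility section). Thirty women randomised 2:1, so 20 and 10 (Abstract; Group allocation). Sample size section: 10% loss to follow-up, about 77 recruited, final groups of 20, about 10 and about 40. The control completion rates below are assumptions; the article gives none.

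**The plan's own figure.** 70 × 1.10 = 77, the stated recruitment target; 70 / 0.90 = 77.8, or 78. The target is reproduced to within one woman. The 65% and 70% cut-points are not derived in the article, so there is nothing to reproduce for them.

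**Step 1: completers needed.** More than 70% of 30 means more than 21, so 22/30 (73.3%); 21/30 is exactly 70% and does not pass. More than 70% of 20 means more than 14, so 15/20 (75%).

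**Step 2: the pooled pass split by arm.** Intervention completers needed = 22 − control completers.

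| Control completers | Intervention completers that suffice | Zone of that rate by the plan's cut-points |
|---|---|---|
| 10/10 | 12/20 (60%) | below 65% |
| 9/10 | 13/20 (65%) | 65–70% |
| 8/10 | 14/20 (70%) | 65–70% |
| 7/10 | 15/20 (75%) | above 70% |

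So the pooled rule is easier on the intervention arm than the same rule applied to that arm alone whenever at least 8 of 10 controls complete.

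**Step 3: another denominator.** If everyone with baseline data counts, with an assumed 22 + 11 = 33, a pass needs 24/33. Then 11/11 controls allow 13/22 (59.1%) and 10/11 allow 14/22 (63.6%), both below 65%.

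**Step 4: chance of a feasible verdict when true intervention-arm completion is 60%.** Let X ~ Bin(20, 0.60), and let Y ~ Bin(10, p) be independent of X, where p is control completion.

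- Intervention arm alone: P(X ≥ 15) = 0.126.
- Pooled: P(X + Y ≥ 22) = 0.171, 0.281, 0.425, 0.508 and 0.596 for p = 70%, 80%, 90%, 95% and 100%.

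**Step 5: the narrower event.** At 20 + 10, a feasible verdict with the intervention arm strictly below 65% requires exactly 12/20 and 10/10. Its probability is P(X = 12) × p¹⁰ = 0.180 × p¹⁰: 0.019, 0.063, 0.108 and 0.180 for p = 80%, 90%, 95% and 100%.

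**Step 6: break-even in expectation.** Setting (2/3)a + (1/3)p = 0.70 gives a = (0.70 − p/3) / (2/3). A pooled 70% corresponds to intervention-arm completion of 65%, 60% or 55% when p is 80%, 90% or 100%.

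**The case against.** **The article never says the arms are pooled.** True. Pooling follows from the unrestricted noun, the Abstract's use of it for all thirty women, and the booklet's heading as an intervention. If only the intervention arm was meant, the sentence still has to say so.

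**Controls can fail too.** They must return the FACIT-F at six time points plus the other questionnaires, out to 6 months, so 100% is the favourable extreme. The plan's 10% loss to follow-up makes 90% a more natural input. This stands, and is why a range is shown.

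**A reader might infer that a failing intervention arm is declared feasible about half the time.** The documents do not support this. A figure near one half (0.51) needs 95% control completion, which the plan does not state, and it counts every pooled pass, including those where the intervention arm reaches 65% or more. Step 5 gives the narrower event.

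**A reader might also infer that the rule hides poor attendance, or leaves no way to tell missed sessions from missed questionnaires.** It does not. Adherence and retention are reported separately, reasons for discontinuation are sought, and interviews sample women for variation in compliance. What remains is that none of this enters the verdict by arm.

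**The narrow middle band and wide interval are small-sample facts.** The band holds two counts at n = 30 (20, 21) and also at n = 20 (13, 14). The exact 95% CI is 54–88% at 22/30 and 51–91% at 15/20; both span all three zones. These are not defects of pooling, and changing the denominator does not cure them.

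**The primary aim covers trial processes as a whole, so control completion is relevant.** Agreed; the fix keeps it as a separate criterion.

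**Conclusion.** The point holds. On its plain reading, the progression rule lets controls, who have no sessions to miss, raise the rate that decides feasibility. By the plan's own numbers an intervention arm at 60% can be declared feasible if all ten controls complete, and one at 65% or 70% can be if nine or eight do. With true intervention-arm completion of 60%, pooling raises the chance of a feasible verdict from 0.13 to between 0.28 and 0.60 over assumed control completion of 80% to 100%.

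This rests on the pooled reading, on arms of 20 and 10, and on controls completing more often than intervention women. Were both arms to complete equally well, the bias would largely vanish. It is a fault in how the decision rule is specified, not in what is collected or reported.

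**What to change.** Reword the progression rule, keeping the 65% and 70% cut-points:

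1. Apply the plan's existing criterion (all sessions and all outcome measures) to women randomised to the behavioural intervention, with that number as denominator.
2. Apply the same cut-points separately to completion of all outcome measures, shown by arm.
3. Require both for a feasible verdict, and give each rate with its exact 95% CI.

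Outcome completion should stay defined as all measures at all time points. Cutting it to one questionnaire at one visit would drop the 6-month follow-up from the decision, and showing it only for both arms combined would again hide a difference between them.

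The cost is one reworded paragraph; sessions and questionnaire returns are already recorded. The intervention-arm rate will rest on about 20 women, so its interval is wider (15/20: 51–91%, against 54–88% for 22/30), and the headline may be less favourable. With about ten controls, one woman moves that arm's rate by 10 percentage points, so it should be read with its interval.
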